## **2 Justification**

This study will investigate the various effects (physiological, neurobehavioral, and motor) of a physiotherapeutic intervention protocol associated with Kangaroo Positioning in a neonatal unit at the University Hospital of the Federal University of Mato Grosso do Sul. The specific aim is to investigate the effect of this protocol on the establishment and maintenance of breastfeeding, respiratory discomfort, muscle tone, body posture, and, particularly, the impact on motor development during the hospital period and the critical months after hospital discharge.

Given the absence of scientific evidence correlating a physiotherapeutic intervention protocol with Kangaroo Positioning using a randomized controlled clinical trial method, this project will provide experimental foundations for evidence-based practice through a feasible protocol for neonatal unit teams' routines. The results of this project may provide scientific

support for implementing the physiotherapeutic intervention protocol associated with Kangaroo Positioning as a procedure to support the protection of child development and the humanized care of preterm newborns.

This project aims to establish an early intervention protocol at the hospital level, and consequently, it will contribute to the Brazilian epidemiological need for more studies focused on early stimulation (BRAZIL, 2016) in hospitalized newborns at risk or with established neurological problems.

### **3 Objective**

#### **3.1 General objective**

To investigate the short- and medium-term effects of a physiotherapy intervention protocol combined with Kangaroo Positioning over ten days on the neuromotor behavior and clinical outcomes of stable preterm newborns hospitalized in a neonatal unit.

#### **3.2 Specific objectives**

To assess the general movements of preterm newborns who received the physiotherapy intervention protocol associated with the kangaroo position and compare them with the preterm control newborns before and after the protocol period, as well as at 12 weeks post-term.

To evaluate the weight gain in preterm newborns who received the physiotherapy intervention protocol associated with the kangaroo position compared to the preterm control newborns.

To analyze posture and muscle tone in preterm newborns who received the physiotherapy intervention protocol associated with the kangaroo position compared to preterm control newborns.

To assess the behavioral state in preterm newborns who received the physiotherapy intervention protocol associated with the kangaroo position compared to preterm control newborns.

To examine the time to establish and maintain breastfeeding in preterm newborns who received the physiotherapy intervention protocol associated with the kangaroo position compared to preterm control newborns.

To evaluate the length of hospital stay in preterm newborns who received the physiotherapy intervention protocol associated with the kangaroo position compared to preterm control newborns.

To assess respiratory distress scores in preterm newborns who received the physiotherapy intervention protocol associated with the kangaroo position compared to preterm control newborns.

To examine physiological parameters (vital signs) in preterm newborns who received the physiotherapy intervention protocol associated with the kangaroo position compared to preterm control newborns.

To compare the effects between preterm newborns who received the physiotherapy intervention protocol associated with the kangaroo position and preterm control newborns.

## **4 Methodology**

### **4.1 Design**

This project is characterized as a controlled, randomized, longitudinal, parallel-group clinical/therapeutic trial.

### **4.2 Participants**

This study will involve 34 preterm newborns, born with a gestational age of 34 weeks or less, between 34 and 36 weeks and 6 days postmenstrual age, hospitalized in the Neonatal Intermediate Care Unit (UCIN). To estimate the minimum number of participants, considering a difference of at least 50% between the groups regarding the quality of general movements (GMs) after the intervention using the chi-square test, the suggested sample size is 13 participants per group (80% power;  $\alpha = 5\%$ ). Considering potential losses during the follow-up, two groups of 17 participants will be included. The newborns will be randomly allocated into two groups: the experimental group ( $n=17$ ), which will receive the physiotherapy intervention protocol associated with the kangaroo position, and the control group ( $n=17$ ), which will receive only the kangaroo position.

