### **4.9 Outcomes**

#### **4.9.1 Primary outcomes**

- **Weight Gain:** daily body weight recording as a parameter for weight tracking of preterm newborns during the application of the protocol (experimental and control).
- **Neuromotor Behavior:** assessed by the classifications of GMs achieved using the GMA (EINSPIELER et al., 1997).

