#### 4.10 Data Analysis

For the statistical analysis of the data, the statistical package SPSS 23.0 will be used. To analyze the dependent variables, the Levene's Test for Homogeneity of Variance and the Shapiro–Wilk Test for Normality will be applied. Once the assumptions are met, parametric and non-parametric tests may be applied depending on the homogeneity and normality conditions of the sample. Descriptive statistics will first be performed to characterize the sample. Treatment effects will be obtained by comparing the groups

To test differences between groups (treatment effects) for categorical variables (quality of GMs, behavioral state, success, and maintenance of breastfeeding), the chi-square test will be applied. To test differences between groups concerning body weight, the independent t-test will be used. For other continuous variables, t-tests or the Mann–Whitney test will be used to calculate differences between the groups. Adjusted means and 95% confidence intervals may also be calculated using the mixed linear model (GLM) for continuous variables, considering the interaction terms of group x days of evaluation.

To calculate the effect size of the intervention, a 95% confidence interval will be adopted, and either Cohen's d or r ( $r = \text{z-score} / \sqrt{\text{total sample}}$ ) will be considered, depending

on whether parametric or non-parametric tests are used. A significance level of  $\alpha=5\%$  will be considered for all analyses.

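### The 13 per group with 80% power at 5% holds only for a two-category GM outcome that the protocol never defines, an absolute 50-point difference and an uncorrected chi-square

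*Protocol*

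**What the plan says.** Protocol 4.2 bases the sample size on "considering a difference of at least 50% between the groups regarding the quality of general movements (GMs) after the intervention using the chi-square test". It concludes that "the suggested sample size is 13 participants per group", with 80% power and a 5% level, and raises this to 17 per group for losses. It does not name the event being compared or give a control rate, and it does not say whether 50% is absolute or relative.

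Section 4.7.1 lists four classes for writhing movements (normal, poor repertoire, cramped-synchronized, chaotic) and three for fidgety movements (normal, abnormal, absent). Section 4.9.1 makes neuromotor behaviour a primary outcome, "assessed by the classifications of GMs achieved using the GMA". Section 4.10 states that "for categorical variables (quality of GMs, behavioral state, success, and maintenance of breastfeeding), the chi-square test will be applied". It mentions no grouping of classes, continuity correction or exact alternative.

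The second research question at the end of section 1 asks about normalising GMs in infants with poor repertoire, and section 4.3 admits only such infants. Both suggest normal versus not normal, but neither section 4.9.1 nor section 4.10 adopts it.

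**The concern.** The sample size statement and the planned analysis describe different tables. A 50-point difference is defined for a 2x2 table. Four writhing classes by two arms is a 2x4 table, with three degrees of freedom and less power for the same shift.

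Reducing the classes to two raises a second question. At 13 per group the uncorrected chi-square is a rough approximation, and the choice between it and an exact test can decide the result. For 4/13 versus 9/13 the chi-square gives p = 0.0499, Boschloo 0.076 and Fisher 0.115. For 3/13 versus 8/13 the chi-square gives 0.047 and Fisher 0.111. If the grouping and the test are not fixed in advance, the primary conclusion could depend on choices made after the data are seen.

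**Working it through.** **Inputs.** From Protocol 4.2: 13 and 17 per group, equal allocation, difference 0.50, power 80%, level 5%. Assumed: two-sided test, difference absolute, control rate p1 varied from 0 to 0.50 because none is given.

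**Step 1: reproduce the 13.** With p2 = p1 + 0.50 and p̄ the mean of the two rates,

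n = [1.96·√(2p̄(1−p̄)) + 0.8416·√(p1(1−p1) + p2(1−p2))]² / 0.50².

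- 0% v 50%: (1.2003 + 0.4208)²/0.25 = 10.5, so 11.
- 8% v 58%: (1.3034 + 0.4740)²/0.25 = 12.6, so 13.
- 10% v 60%: (1.3221 + 0.4835)²/0.25 = 13.04, so 14.
- 25% v 75%: (1.3859 + 0.5154)²/0.25 = 14.5, so 15.

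The stated 13 is within two infants at every control rate and exact at about 6% to 9%. Three other readings fit less well:

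- A one-sided test gives 9 to 12.
- A continuity correction gives 15 to 19.
- A relative 50% gives, for example, 42 for 60% v 30%, where the chi-square has 41% power at 13 per group.

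**Step 2: two categories, exact enumeration of all 2x2 tables.** Power for a 50-point difference:

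| Rates | Chi-square, n=13 | Fisher, n=13 | Fisher, n=17 |
|---|---|---|---|
| 0% v 50% | 95% | 87% | 98% |
| 5% v 55% | 87% | 76% | 88% |
| 10% v 60% | 84% | 71% | 83% |
| 25% v 75% | 82% | 68.5% | 79% |

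At 13 per group Fisher has 81% power at 2% v 52%, so it reaches 80% only at control rates of about 2% or lower (or at the mirror image, an experimental rate of about 98% or higher). Boschloo's test has 69% at 25% v 75%.

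**Step 3: type I error of the uncorrected chi-square.** At 13 per group, by common rate: 1.8% at 0.10, 4.96% at 0.25, 5.65% at 0.30, 7.0% at 0.40 and 7.56% at 0.50. It exceeds 5% between about 0.26 and 0.74. The maximum over all common rates is 5.2% at 14 per group, 5.5% at 15, and 5.8% at 16 and 17. Fisher's maximum at 13 per group is 2.9%.

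Steps 2 and 3 are linked. At 25% v 75% the formula in step 1 gives 75% power at 13 per group, while exact chi-square power is 82%. The average rate there is 0.50, which is where the test exceeds its nominal level most.

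**Step 4: classes as defined.** Power was simulated for the Pearson test on assumed splits that keep a 50-point shift in the normal class.

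- Four classes, 13 per group: 57% (25/25/25/25 v 75/8.3/8.3/8.4), 64% (25/60/10/5 v 75/20/3/2) and 69% (25/60/10/5 v 75/15/5/5). At 17 per group the first two give 72% and 76%.
- Three classes, 13 per group: 64% (25/37.5/37.5 v 75/12.5/12.5) to 75% (10/80/10 v 60/35/5). At 17 per group, 79% to 85%.
- In the null scenarios run, these tests rejected 3% to 4% of the time, so no inflation was seen.

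**The case against.** A reader might infer that the sample size arithmetic is wrong. It is not: 13 follows from the standard formula, and the named test has at least 80% exact power on a binary outcome with a 50-point difference.

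A reader might also take 7.6% as the error rate of the planned test. It is the peak at exactly 13 per group in both arms with a common rate near one half. At 13 per group the error stays at or below 5% for common rates up to about 0.25, and at 14 to 17 per group it is at most 5.8%. It also belongs to the 2x2 table, whereas the power loss from several classes belongs to the larger tables. The two problems are alternatives and do not add up.

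Three further inferences lack support:

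- **That only 26 infants can be analysed.** Section 4.2 gives 13 per group as a minimum and enrols 34.
- **That the usual expected-count condition cannot be met for three classes.** With equal arms, an expected count of 5 in every cell needs 10 infants per class. Three classes need 3 × 10 = 30, which is within 34. The condition is also only a convention.
- **That 80% power was claimed at 12 weeks post-term.** Section 4.2 refers to GMs after the intervention and makes no claim for the later visit.

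The remaining defence is that the second research question implies normal versus not normal, that unused classes would collapse the table, and that a statistical analysis plan could settle this. That has some force. But the protocol itself states the outcome, the test and the power, and these do not fit together. Letting the observed classes decide the table would leave the primary analysis open until the data are in. Fisher's conservatism does account for part of its lower power.

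**Conclusion.** The point holds as a mismatch between the stated sample size and the stated analysis. The figure of 80% power at 5% belongs to a two-category outcome that sections 4.9.1 and 4.10 do not define.

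- **In classes as written:** 57% to 75% power at 13 per group. This rests on the assumed splits. At 17 per group three classes come to about 80%, but the two four-class splits run there stay below it.
- **As two categories with the uncorrected chi-square:** the power is there, but at 13 per group the 5% level is not held for common rates between about 0.26 and 0.74.
- **As two categories with Fisher's test:** the level is held, but at 13 per group power is below 80% unless the control rate is about 2% or lower. At 17 per group it is 79% or more.

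The two-category figures assume an absolute 50-point difference and equal numbers analysed per arm. The true control rate is unknown. Because every infant enters with poor repertoire, a low rate of normalisation in controls is possible, and the shortfall would then be smaller.

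**What to change.** - **4.9.1:** define the post-protocol primary GM outcome as normal versus not normal. The full classes can still be tabulated descriptively.
- **4.10:** for this outcome, replace the chi-square with an exact test at the 5% level (Boschloo, or Fisher in SPSS). Report the risk difference with an exact or score 95% confidence interval.
- **4.2:** say that 50% means percentage points (absolute). Restate worst-case Fisher power (25% v 75%) as about 69% with 13 and 79% with 17 evaluable per group. Because exact tests move in steps, the figure for 13 is not a lower bound: at 14, 15 and 16 per group it is 63%, 67.5% and 74%.

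The cost is wording in three sections and no extra infants. The quoted power becomes less favourable, and if Fisher is chosen its conservatism must be accepted. The changes should be made before the GM recordings are compared by group.

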### **4.3 Inclusion criteria**

Preterm newborns will be included in the study if they meet the following criteria: gestational age at birth equal to or less than 34 weeks, more than 72 hours of postnatal life, hospitalized in the Neonatal Intermediate Care Unit (UCIN), clinically stable, general

movements with a poor repertoire, no need for invasive or non-invasive mechanical ventilation, may require oxygen support via nasal cannula, residents of Campo Grande-MS (Brazil).

Medical records, nursing notes, physiotherapy records, and the recommendations from neonatologists and the multidisciplinary team will be used as the reference for the selection or exclusion of patients based on the criteria described above.

#### **4.4 Exclusion criteria**

Preterm newborns will be excluded from the study if their gestational age at birth is equal to or greater than 34 weeks and 1 day, or if they have any of the following conditions: congenital malformations, chromosomal syndromes, active infections under treatment (with altered blood count or positive blood culture), neurological problems (such as grade III or IV intraventricular hemorrhage or brain malformations), neonatal asphyxia (with an Apgar score of less than 7 at the fifth minute), or congenital infections. Additionally, newborns will be excluded if they have any contraindications to performing the physiotherapy intervention protocol or the kangaroo position.

They will also be excluded if their parents or guardians do not consent to the newborn's participation in the study or request their withdrawal. If the newborn experiences adverse reactions to the physiotherapy protocol or kangaroo positioning, such as clinical instability during the procedure (e.g., cyanosis, crying, lethargy, signs of pain, generalized erythema) or in the short and medium term (e.g., worsening of the clinical condition, feeding intolerance, or behavioral disturbances), they will be excluded. Moreover, newborns may also be excluded if complications arise that prevent the application of the protocol, such as the need for invasive or non-invasive mechanical ventilation, oxygen therapy via a Hood Box, or the requirement of surgical procedures.

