#### 4.7.3 Brazelton's Neonatal Behavioral State

The adapted Brazelton's Neonatal Behavioral Assessment Scale was used to assess behavioral state. The scale categorizes the newborn's behavior based on their current state,

ranging from 1 to 6. State 1: deep sleep, still with steady breathing; State 2: light or active sleep, eyes closed with occasional body movements; State 3: drowsy, intermittently opening and closing the eyes; State 4: quietly alert, minimal physical activity; State 5: fully awake with energetic movements (active alert); State 6: crying (BRAZELTON et al., 1976).

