#### **4.8.2 Procedures of randomization and allocation**

The distribution of newborns into groups will be random, following a prior computational randomization in blocks of 4 babies for each group. The allocation to the groups will be concealed from the researchers involved through individual opaque, sealed, and sequentially numbered envelopes. The envelopes will be opened before the experimental or control protocol is performed, according to the inclusion of the babies in the study. The evaluations for GMs will be filmed and scored later, without identifying the allocation of the newborns in the groups, allowing for a subsequent blinded assessment.

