##### *4.8.4.1. Assessments at the UCIN*

The preterm newborns in both the experimental and control groups will be evaluated by the researcher in the NICU regarding respiratory discomfort at two time-points: I) before the

start of the protocol (experimental or control), with the baby still in the incubator/crib (Day 1); and II) after the completion of the protocol with the baby positioned in the incubator/crib (Day 15).

Physiological parameters (heart rate, respiratory rate, peripheral oxygen saturation, body temperature) and behavioral state will be assessed at three-time points daily: I) immediately before the protocol (experimental or control), with the baby still in the incubator/crib; II) 60 minutes after the start of the kangaroo position (experimental or control), while the baby remains in the position; and III) 30 minutes following, with the baby repositioned in the incubator/crib.

GMs and neuromotor screening (posture and tone) will be evaluated at two time-points: I) one day before the start of the protocol; and II) one day after the completion of the protocol.

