#### *4.8.5.1 Physiotherapeutic intervention protocol*

The physiotherapeutic intervention protocol will be applied only to the experimental group. The intervention will consist of the following handling techniques: I) Lumbosacral pumping; II) Posterior stretching; III) Cervical muscle stretching; IV) Thoraco-humeral dissociation; V) Therapeutic exercise to feel the head with the hands; and VI) Positioning in supine to allow spontaneous movements of the preterm newborn. The protocol begins with lumbosacral pumping while the newborn is in a supine position with the head slightly flexed. The therapist's right hand is positioned on the lumbosacral region, and the left hand supports the anterior pelvic region. Using the right hand's middle and ring fingers, the therapist gently pulls in a caudal direction (GONÇALVES, 2012; BUSQUET-VANDERHEYDEN, 2009); without losing pelvic retroversion, the newborn is moved to a lateral position, and posterior stretching is performed with the right hand on the sacral region and the left hand positioned under the occipital bone, performing subtle, passive traction on both sides of the vertebral axis during expiration (LIMA, 2012; BUSQUET-VANDERHEYDEN, 2009). After this handling, cervical stretching is performed with the therapist's right hand holding the shoulder and the left hand supporting the occipital and temporal regions. The newborn is raised to approximately 30°, the head and neck are gently slid to the right side, while the left shoulder is softly lowered. The shoulder is released, and the head is returned to the midline. The hands are reversed, and the movement is performed on the opposite side (DUARTE et al., 2011); immediately after this handling, thoraco-humeral dissociation is performed, where the therapist uses one hand to hold the shoulder region and makes circular movements in a postero-anterior direction (LIMA, 2012); in the exercise to feel the head with the hands, the newborn remains in a supine position, with the cervical spine straightened, trunk and lower limbs flexed, and the newborn's hands are moved to the parietal region, sliding the palms of the hands forward and laterally over the face, rubbing them in front (DUARTE et al., 2011); to finish, the newborn will be positioned in a supine position in the incubator/crib, allowing spontaneous movements with the nest slightly away. The protocol will last 15 minutes, and immediately afterward, the newborn will be placed in the kangaroo position with the mother for 60 minutes.

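### Section 4.4 removes randomised newborns from the study because they reacted badly to treatment; it should stop the treatment and keep them in their allocated group with the scheduled assessments

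*Protocol*

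**What the plan says.** Section 4.4 opens by listing who is excluded from the study on baseline grounds, then adds grounds that can arise only once treatment has begun. The consequence is the same whether a newborn reacts badly to the physiotherapy or the kangaroo position at once "or in the short and medium term (e.g., worsening of the clinical condition, feeding intolerance, or behavioral disturbances), they will be excluded". For immediate reactions the section gives this description and these examples: "such as clinical instability during the procedure (e.g., cyanosis, crying, lethargy, signs of pain, generalized erythema". A further sentence adds that infants may also be excluded for complications such as ventilation, Hood Box oxygen or surgery.

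The other relevant provisions are:

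- **Timing** (4.8.2): "The envelopes will be opened before the experimental or control protocol is performed".
- **Exposure** (4.8.5.1): "The physiotherapeutic intervention protocol will be applied only to the experimental group". Controls receive the same kangaroo positioning without it (Control protocol section).
- **Who decides**: no section names a decision-maker for exclusions during treatment. Section 4.3 says that clinical records and "recommendations from neonatologists and the multidisciplinary team will be used as the reference for the selection or exclusion of patients".
- **Blinding** (4.8.2): "The evaluations for GMs will be filmed and scored later, without identifying the allocation of the newborns in the groups". No other blinding is described.
- **Outcomes**: weight gain and general movements (GMs) are primary (4.9.1). Behavioural state and vital signs are secondary (4.9.2) and are recorded daily, including "60 minutes after the start of the kangaroo position (experimental or control), while the baby remains in the position" (4.8.4.1).
- **Overload signs** (section 5, Risks and Benefits): the only action prescribed is to interrupt the handling and let the newborn reorganise.

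No section says that an excluded newborn continues to be assessed or is analysed as randomised. Section 4.10 says only that the groups will be compared.

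**The concern.** Randomisation makes the two arms comparable only while membership of the comparison does not depend on what happens after allocation. Here it does: an infant leaves because of how it responded to treatment. The arms are not equally exposed to the triggers, since the stretching, traction and handling occur in one arm only. The people likely to decide are at the cotside and know the allocation.

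Several triggers also lie close to what the trial measures. Crying is the top category of the behavioural-state scale in 4.7.3 ("State 5: fully awake with energetic movements (active alert); State 6: crying"). Feeding intolerance bears on weight gain, a primary outcome. Cyanosis and clinical instability bear on the hypothesis, stated in the Introduction, that vital signs stay safe. Removing infants for these reasons can make the treatment look both more effective and better tolerated than it is.

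This is more than an analysis detail that a statistical analysis plan could settle. If an infant leaves the study, its later weights and GM videos are never collected, and no analysis rule can recover them.

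**Working it through.** **1. Does the rule act after randomisation?** Reactions to the protocol require the protocol to have started (4.4). The envelope is opened before that (4.8.2). So every infant removed under this sentence has already been allocated.

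**2. Does the protocol treat every such sign as a reason to leave?** Crying and cyanosis appear in 4.4 as grounds for exclusion. In section 5, crying and perioral cyanosis appear as overload signs that call only for interruption. The two sections prescribe different consequences for overlapping signs.

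**3. The plan's sample size and loss allowance.** Section 4.2 gives 13 per group (80% power, 5% level, chi-square, a difference of 50 percentage points), raised to 17. The base rates are not stated. Using

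n = [1.96·√(2p̄(1−p̄)) + 0.842·√(p₁(1−p₁) + p₂(1−p₂))]² / 0.50²

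- 5% vs 55%: 11.9, so 12
- 10% vs 60%: 13.04, so 14
- 25% vs 75%: 14.5, so 15

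The stated 13 falls within this range. The loss allowance is 17 − 13 = 4 per arm, used below as a plausible upper number of removals.

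**4. Shift in the observed proportion with no treatment effect.** Assume half of infants are normal in both arms, so 8.5 of 17 are expected to be normal. If the experimental infants removed all have abnormal GMs:

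- two removed: 8.5/15 = 56.7%, a shift of 6.7 points
- four removed: 8.5/13 = 65.4%, a shift of 15.4 points

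**5. False-positive rate.** Method: exact enumeration of two independent Binomial(17, p) counts with equal p, removing up to k abnormal infants from the experimental arm, two-sided Pearson chi-square at 5% without continuity correction. The normal rate p and the number k are assumptions.

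| Normal rate in both arms | k = 0 | k = 2 | k = 4 | 4 experimental and 2 control removed |
|---|---|---|---|---|
| 25% | 4.5% | 6.1% | 9.2% | 7.0% |
| 50% | 5.8% | 7.7% | 15.9% | 13.0% |
| 75% | 4.5% | 14.4% | 30.5% | 16.3% |
| 90% | 3.1% | 6.4% | 6.8% | 0.5% |

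Nearly all of the excess favours the experimental arm. At 50% normal, false positives in its favour rise from 2.9% to 15.4% with four removed.

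**6. Reference case.** If four experimental infants are removed for reasons unrelated to outcome (13 vs 17), the rate is 5.3%, 4.7% and 5.3% at 25%, 50% and 75% normal. The bias comes from selective removal, not from the smaller arm.

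**7. Test variant.** Section 4.10 says only chi-square. With a continuity correction the rates for k = 0, 2, 4 are 1.7%, 2.1%, 3.8% at 25% normal; 2.4%, 3.8%, 9.3% at 50%; 1.7%, 5.1%, 11.0% at 75%; and 0.2%, 0.4%, 0.4% at 90%. The levels are lower, but removal still inflates them relative to k = 0.

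**8. Power if stopped infants are kept.** Assume 25% vs 75% normal and, as a worst case, that stopped infants respond at the control rate. By exact enumeration with 17 per arm:

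| Experimental infants affected | Expected difference if kept | Power if kept | Power if excluded at random |
|---|---|---|---|
| 0 | 50.0 points | 88% | 88% |
| 2 | 50 × 15/17 = 44.1 points | 79% | 85% |
| 4 | 50 × 13/17 = 38.2 points | 66% | 81% |

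**The case against.** The strongest reply is that the bias is conditional and the protocol does not show that it will occur. The rule covers reactions to either component, so control infants can be removed too, and no reaction rate is given for either arm. The largest figure, 30.5%, is close to a worst case: at 75% normal only 17 × 0.25 = 4.25 abnormal infants are expected in the arm, so removing four takes out nearly all of them and presumes an almost perfect link between reaction and outcome. The four spare infants in 4.2 are meant for losses to follow-up in general, not for adverse reactions alone. With a continuity correction, many of the rates sit at or below 5%. It can also be said that section 5 implies a graded response, that readings taken before exclusion need not be discarded, and that the analysis population may be defined elsewhere.

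Most of this bears on weight and is accepted: the figures are illustrations, and unequal removal is foreseeable rather than demonstrated. It does not answer the main point. The text prescribes removal from the study because of response to treatment, in arms that are not equally exposed, and nothing in the protocol provides for data collection after removal. A graded reading is sensible, but 4.4 does not state it.

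Two practical objections to the remedy also stand. The following sentence, on complications, has the same defect and should be covered. The planned end of the protocol must also be a fixed day, because the Abstract and 3.1 give ten days while the Introduction, 4.8.4.1 and 4.8.5.2 give fifteen.

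**Conclusion.** The concern holds. As written, section 4.4 removes randomised newborns because of how they reacted to treatment, and the experimental arm carries an extra source of such reactions. The likely direction of bias favours the experimental arm, provided that infants who tolerate handling badly are also less likely to normalise their GMs or to gain weight. That link is plausible but is not shown in the document.

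The size cannot be fixed from the protocol. With up to four selective removals from the experimental arm and none from control, the uncorrected chi-square gives false-positive rates between 6.1% and 30.5% over the base rates tried, against 3.1% to 5.8% with none removed. With removals in both arms the rates are mostly lower, and if removal is unrelated to outcome there is no inflation. No figure is offered for weight gain, because the protocol gives no variability for it.

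The rule should be changed. With 17 infants per arm each removal matters, and data not collected cannot be restored at the analysis.

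**What to change.** In section 4.4, keep the baseline exclusions and replace the exclusion for adverse reactions with wording such as:

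> If a reaction occurs, the session is interrupted as described in section 5. The intervention is stopped if the reaction persists or recurs, or if the neonatal team judges it unsafe to continue. A newborn whose intervention is stopped remains in its allocated group for analysis. Its weight is recorded to the planned final day, and its GMs are assessed on the day after that date and at 12 weeks post-term, unless consent is withdrawn.

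Apply this to both arms, record each stop with its date and reason, and extend the same wording to the sentence on complications. State the planned final day as one number. The neonatal team keeps full discretion to stop for any sign, crying included.

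Costs: this changes a stopping rule, so it needs an amendment and ethics review. It adds no new type of assessment, since weight and both post-baseline GM assessments are already scheduled for every infant (4.8.4 to 4.8.4.2). Keeping infants with incomplete treatment dilutes the effect. In the worst case worked above, power falls from 88% to 79% with two stopped and 66% with four, the last well below the planned 80%. Exclusion at random would have left 85% and 81%. That loss is the price of a comparison that includes the infants who could not tolerate the treatment.
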